### Objective SHS measures

Parents and carers have the option of collecting child saliva samples and/or having air quality measured in their home, unless they care for one child in the home under the age of 5, in which case we will measure air quality in their home. We are also measuring air quality in the home of non-parental carers who agree to take part, but they do not have the option of obtaining saliva samples from the child, because parental consent is required for this.

We are assessing the feasibility of participants collecting and posting saliva samples from their youngest child (aged 5 or over) for cotinine analysis. Biological markers of SHS exposure are viewed as the ‘gold standard’,^37 38^ and salivary cotinine is widely accepted as the best biological indicator of SHS exposure. It is commonly collected in studies of children’s exposure to SHS in the home. It provides information on recent (hours–days) exposure to SHS, so it is well suited to our study given our baseline to follow-up period spans 12 weeks, and it can also quickly reflect change in household smoking behaviours. Other research^39^ has suggested that posted cotinine samples may be a reliable option for verifying adult tobacco use, and COVID-19 has made careful self-collection of biological samples using detailed instruction a much more common task among the public. If self-collected, posted saliva cotinine samples can be demonstrated to be a reliable way to gather data on SHS exposure, we will use this lower-cost method of collection in our future definitive trial, using a reduction in children’s salivary cotinine levels (comparing samples taken at baseline and 12-week follow-up) as our primary outcome measure. This finding would have also benefits for other work, including the SHeS which currently involves in-person visits for saliva collection.

Changes in indoor PM_2.5_ levels between baseline and follow-up (collected by air quality monitors) could provide an alternative method of determining changes in smoking behaviours in a larger trial, so we are also assessing the feasibility of participants measuring air quality and posting air quality monitors. We obtain consent from participants to measure indoor air quality for a 1-week duration, using a PurpleAir Flex air-quality monitoring device, at baseline and follow-up. The team member oversees participant installation of the air quality monitor during the initial home visit, using simple instructions for self-installation we have developed in our previous studies. Participants are asked to switch it on in the main living room of their home for a 1-week duration, to gather data on in-home PM_2.5_ concentrations at baseline (measuring PM_2.5_ is an internationally recognised, widely used method of quantifying SHS in the air).^38^ At the end of week 1, they receive a prearranged call from the researcher reminding them to return the monitor via a second prepaid postage box or a researcher visit if more convenient. During the home visit, parents who choose to also collect a sample of saliva for analysis of cotinine levels from their youngest child (aged 5 or over) use printed instructions (without input from the researcher). The team member collects a second sample from the same child immediately afterwards, essentially providing training to the participant on how to collect the sample for the follow-up sample in 12 weeks’ time. Each participant is asked to post the saliva sample they obtain back to the study team to test the feasibility of this part of the process. The study team member takes the saliva sample they obtain with them at the end of the home visit.

If initial evidence (after approximately 10 weeks of baseline data collection) suggests that these baseline, self-collected samples are returned through the post (>90%) and have sufficient saliva volume (>90%), this will provide us with the option of participants collecting and posting the second sample of saliva from the same child at follow-up. If these criteria are not met, we will gather data through in-person home visits and team member sample collection.

Each participant obtaining air quality measures in the home also receives the air quality monitor again at follow-up, and a second 1-week duration of measurement will be taken. All sampling/monitoring equipment is posted to the home at no expense to participants. Sampling sheets are used to record sample/monitor ID number (also on the saliva sample tube), the participant ID number and to confirm the child’s assent was obtained for providing saliva samples. We compare PM_2.5_ concentrations at baseline and Week 13. Participants can opt in to receive a lay summary of findings, including average baseline and follow-up salivary cotinine levels and PM_2.5_ levels for each group, at the end of the study. This lay summary will be co-designed with input from our public involvement groups. All participants receive two £25 supermarket vouchers of their choice for taking part in the study—the first after completing the 6-week process evaluation questionnaire by telephone, and the second at the end of the 12-week study. 

20 Group A and 5 Group B participants are taking part in qualitative telephone interviews conducted from week 13 to explore intervention experience, NRT use and adherence, and changes to smoking in the home, smoking consumption and smoking-related expenditure.

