### Eligibility criteria

Parents, carers and relatives who are at least 18 years old, smoke in the home and care for one or more children in the home, aged 0–16 years, at least 1 day per week, are eligible to participate. Multiple family members can participate in the study. Individuals who are interested in taking part but live with another adult smoker who does not wish to, are able to participate. SHS exposure is additive and linear—so we will be able to identify reductions in the number of cigarettes smoked through reductions in fine particulate matter (PM_2.5_) and/or salivary cotinine, even if another adult continues to smoke in the home. While obtaining a completely smoke-free home would not be viable in such cases, it would still be possible to reduce children’s exposure to SHS, which aligns with the aim of the study. Individuals who are not able to understand or speak English as their primary language are excluded given we do not have a budget to recruit, train and pay bilingual staff.

Individuals who use warfarin, theophylline or aminophylline, clozapine, erlotinib, olanzapine, riociguat, chlorpromazine, flecainide or methadone are excluded as NRT use would require general practitioner monitoring. Pregnant and breastfeeding women are excluded from participation as the NRT products offered are only licensed for this group of people who are making a quit attempt. Participants who have a hypersensitivity to nicotine or any components of the nicotine replacement products offered in this study and listed in the product literature are excluded from taking part—we establish this by asking specific questions regarding any previous use of NRT and whether participants have any allergies.

Reasons for participant ineligibility are recorded, and an informed consent process is followed during recruitment. Eligible individuals read the information sheet, or have it read to them, detailing the purpose of the trial and study procedures, potential benefits and risks of participation, data handling procedures, participant rights and relevant contact details. In the event that an individual loses capacity during participation in this research, we will retain all data up to the point of removing the participant from the study. This is also made clear in the participant information sheet.

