Following methods used in the annual health survey in England for collection of child saliva samples, if parents choose this option, they are required to provide written consent for the collection of saliva samples from their youngest child aged 5 or over. A copy of the completed consent form is posted to all participants. We provide each participant with an age-appropriate information sheet by post for them to share and discuss with their child in advance of a prearranged home visit from a member of the NHS intervention delivery team. During this visit, the child is required to assent to the sample collection for it to proceed. The process for gaining assent from the child also follows those used in the annual health survey in England. Parents are required to give fully informed consent. Assent from children indicates that they have been given an age-appropriate explanation that they can understand (even if not as comprehensive as for an adult), and that the child is happy for the procedure to go ahead.^33^ Children are not required to sign anything, but the NHS Lanarkshire intervention delivery team member signs an ID form to confirm the child’s assent has been obtained during the home visit. With permission, (and in the case of parents, if they choose to have air quality measured in their home), the team member also instals an air quality monitor during this visit, to measure PM_2.5_ levels in the home for 1 week.

A suitable date/time is agreed during this home visit for the same team member to telephone each participant after 1 week, to initiate intervention delivery. Participants are randomised (1:1) to either the intervention (Group A) or control (Group B) arm prior to this telephone call. If more than one individual from the same family participates in the study, each family member is allocated to the same study arm.

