### Sample size

We have drawn on published work to guide our sample size, which outlines a median sample size per arm of 36 for pilot RCTs with similar primary outcome measures.^34^ We have also considered the relatively homogenous nature of our sample in terms of deprivation and ethnicity, our intention to conduct qualitative interviews with low and high adherers, resources and costs. On this basis, we aim to recruit 100 participants, to have approximately 35 in each group (allowing for a 30% drop-out rate). 

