### Data analysis plan

Descriptive data analyses will be performed to address the feasibility objectives. Child saliva samples will be processed for salivary cotinine by a specialist, accredited laboratory. The research team will analyse data from the air quality monitors. We will report the percentage of participants that return a valid (sufficient saliva) sample through self-collection, and the level of agreement between the self-collected and researcher-collected salivary cotinine values at baseline to determine the suitability of self-collection of these samples. Analysis will also include pre/post changes (paired t-test) in both child’s salivary cotinine and PM_2.5_ levels to provide preliminary data on intervention effectiveness and difference between the intervention and control arms of the study. Data on variability in these objective measures will also help calculate suitable sample size for the future trial. The qualitative data from the 6-week process evaluation questionnaire will be analysed using content analysis. All qualitative interviews will be recorded with participant permission, transcribed, anonymised and analysed using the framework approach. Transcripts and recordings will be stored securely and destroyed in line with University of Stirling procedures, taking account of General Data Protection Regulation. The health economics and resource use data will be assessed for completeness, to test the process of data collection and the mean cost of both study arms estimated. We will assess suitable outcomes and identify key drivers of uncertainty for any future economic evaluation in a large-scale trial. We will consider the suitability of data to inform a cost-consequence analysis (particularly suitable for public health interventions with multiple possible benefits) and conduct this analysis, to provide information on where further focus might be beneficial in a future definitive trial. 

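### Change in living-room PM2.5 is read as change in secondhand smoke through a within-arm pre/post test that background shifts can move, and no comparison with cotinine is stated

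*Protocol article*

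**What the plan says.** The Abstract (Methods and analysis) presents both the air monitor and child salivary cotinine as ways of putting a number on the child's exposure to secondhand smoke (SHS). Under Objective SHS measures, "Participants are asked to switch it on in the main living room of their home for a 1-week duration", once at baseline and again at follow-up. The same section says that measuring PM2.5 "is an internationally recognised, widely used method of quantifying SHS in the air", and that change in PM2.5 "could provide an alternative method of determining changes in smoking behaviours in a larger trial". It calls cotinine the best biological indicator and names it as the intended primary outcome of the definitive trial, provided that posted self-collection proves reliable.

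Eligibility criteria states that "SHS exposure is additive and linear" and concludes that fewer cigarettes smoked will be visible through lower PM2.5 and/or cotinine, even where another adult goes on smoking.

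The Data analysis plan covers "pre/post changes (paired t-test) in both" cotinine and PM2.5. It offers these as preliminary information on effectiveness and on the difference between arms, and no other test is named. It plans to use the variability of the two measures to size the next trial. The one agreement analysis compares baseline cotinine from parent-collected and staff-collected samples. Parents with a child aged 5 or over may choose saliva, air monitoring or both.

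**The concern.** PM2.5 is a particle-size fraction, not a tobacco-specific marker. Outdoor air, cooking and heating can all contribute, and the article mentions none of them. Two things follow.

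First, a paired pre/post test within an arm takes in whatever else changed between the two monitoring weeks. Those weeks are about 12 to 13 weeks apart, enough for season or household habits to shift. A fall in background would look like less smoking, and a rise would hide a real reduction.

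Second, the pilot asks whether PM2.5 could stand in for cotinine later, but what it states it will assess is whether monitors can be used and returned. Successful posting does not show that PM2.5 change follows the child's exposure. Smoking might, for example, only move out of the living room. Families who give both measures could inform that question, and the article states no analysis that uses them so.

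**Working it through.** **The plan's own figure.** Sample size gives 100 recruited, about 35 per arm after 30% drop-out. 70 / (1 − 0.30) = 100, and 100 × 0.70 / 2 = 35. It reproduces and is not affected by this point. The article gives no PM2.5 level, SD or correlation, so every input below is an assumption.

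**Model.** Total PM2.5 = smoke + background. This is this review's step. The additivity statement in Eligibility criteria concerns other smokers in the home, not other sources of particles.

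**1. Absolute change, stable background.** Smoke 10 and background 10 µg/m³ fall to 5 and 10. The total changes by 20 − 15 = 5, which is the true smoke change. There is no bias.

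**2. Percentage change, stable background.** If a share b of baseline PM2.5 is not smoke and smoke falls by r, the observed fall is r × (1 − b). For r = 50%:

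| b | Observed fall in total |
|---|---|
| 0.10 | 45% |
| 0.25 | 37.5% |
| 0.40 | 30% |
| 0.60 | 20% |

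**3. Background shift common to both arms.** Take b = 0.25, a true smoke fall of 50% in Group A and 10% in Group B, and a background shift s, all as a share of baseline total. Change in A = −0.75 × 0.50 + s. Change in B = −0.75 × 0.10 + s.

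| s | Within A | Within B | A minus B |
|---|---|---|---|
| 0 | −37.5% | −7.5% | −30 points |
| −10% | −47.5% | −17.5% | −30 points |
| −20% | −57.5% | −27.5% | −30 points |
| +10% | −27.5% | +2.5% | −30 points |

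The within-arm figures move with s and the between-arm difference does not. That protection comes from randomisation: "Participants are randomised (1:1) to either the intervention (Group A) or control (Group B) arm".

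**4. Noise.** Background changes that vary between homes independently of arm widen the SD by √(1 + k), where k is their variance relative to that of smoke change. For an assumed effect of 0.67 smoke-change SDs, 35 per arm all with PM2.5, and a two-sided 5% level, approximate power is 0.80 at k = 0, 0.71 at k = 0.25, 0.63 at k = 0.5 and 0.51 at k = 1.

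**5. What a cotinine comparison could show.** Fisher-z interval: tanh(atanh(r) ± 1.96/√(n − 3)). With r = 0.5 and n = 20, atanh(0.5) = 0.549 and 1.96/√17 = 0.475, giving 0.07 to 0.77. With n = 35 the interval is 0.20 to 0.71.

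**The case against.** The strongest reply is that a condensed article need not describe sensor processing. On the monitors, the Data analysis plan says only that the research team will analyse their data. A reader might infer that uncorrected values will be used and that PM2.5 will never be compared with cotinine. The article supports neither: it states no correction and no comparison, and the full protocol or SAP may contain them. This part of the reply stands.

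A reader might also infer that the smoke effect will be mis-sized. That goes too far. The article speaks of PM2.5 levels and concentrations, which suggests absolute change, and stable background cancels there (step 1). The dilution in step 2 applies only if changes are reported as percentages or on a log scale. A shift common to both arms cancels in expectation between arms (step 3). Recruitment runs from January 2024 to September 2025, so background shifts need not all share a sign.

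The variance argument is limited too. If total PM2.5 were the later trial's outcome, the SD of its change is the right one for sizing that trial. Step 4 shows a cost in precision, not an error.

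Finally, the stakes are modest. The primary objective is feasibility, cotinine is the intended later outcome, the wording on PM2.5 is conditional, and no criterion in Table 1 uses PM2.5 change.

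What the reply does not remove is that the one test the article names is the within-arm contrast, which background shifts do affect, and that the one agreement analysis it names does not concern PM2.5.

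**Conclusion.** The point holds in a limited form. As described, the paired test on PM2.5 cannot separate a change in smoking from a change in background. In the illustration, a true arrangement giving −37.5% in Group A reads anywhere from −57.5% to −27.5% for common shifts of −20% to +10% of baseline, while the between-arm difference stays at −30 points. These sizes rest on an assumed 25% background share and assumed smoke reductions, and the documents give nothing to narrow them.

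Separately, the article proposes PM2.5 as a possible alternative measure without stating any comparison with the measure it regards as best. The pilot as described may therefore show that PM2.5 can be collected without informing whether its change tracks exposure. The randomised comparison in absolute units is not biased in expectation by background common to both arms.

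**What to change.** In the Data analysis plan:

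1. Base the PM2.5 effect on the between-arm difference in change, with a confidence interval, and keep within-arm changes as description. As a sensitivity analysis, adjust for outdoor PM2.5 at the nearest public station during each home's monitoring weeks. Report unadjusted and adjusted results side by side.
2. In families with both measures, report the correlation between PM2.5 change and cotinine change with its confidence interval. Treat it as supporting information, not as a pass/fail criterion.

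In the Abstract:

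3. Describe PM2.5 as an indirect marker of SHS in the living room, and drop the implication that it measures the size of the child's exposure.

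The cost is analysis time, using data already being collected plus public outdoor readings. There are limits. Outdoor adjustment leaves cooking and heating particles in place. The families with both measures are an optional group of unstated size, made up only of parents with a child aged 5 or over, so the correlation will be imprecise (step 5). It will also be weakened by timing: baseline saliva is taken at the visit when the monitor is installed and reflects the preceding hours to days, so it comes before the monitoring week.

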### Pilot outcome measures and progression criteria

The following data will be analysed to address the primary (feasibility) objectives of the pilot trial: 

Recruitment, randomisation and retention: Number of participants screened, eligible and successfully recruited into the study, and the characteristics of non-consenting and ineligible participants; number of participants enrolled in the allocated recruitment time; retention of participants in their trial arms following randomisation, the proportion engaging in 12-week follow ups and number/reasons for dropping out. Intervention delivery: The proportion of participants: (1) receiving NRT and demonstrating their adherence to NRT at fortnightly follow-ups; (2) using their personalised plan to identify and address barriers to creating a smoke-free home; and (3) engaging in fortnightly telephone support calls.  Data collection methods: Proportion of completed baseline and follow-up assessments in each arm; number of participants successfully providing child saliva samples and measuring air quality at baseline and follow-up. 

Our final range of secondary outcomes includes number of cigarettes smoked per day (in general and in the home), home smoking practices, self-reported quit attempts and nicotine dependence. 

We have developed progression criteria with input from our Study Advisory Group members, in line with current guidance.^40^ We are using the red/amber/green traffic light system^41^ to guide the decision on whether to progress to a definitive future trial using the criteria presented in table 1.

**Table 1 T1:** Progression criteria.

% of sample size recruited	100% (35 in each arm)	70% or more (25 in each arm)	Less than 70%
% of follow ups completed (SHS measures)	70%	60–69%	Less than 60%
% of participants who try using NRT and engage with at least one fortnightly telephone call	70%	60–69%	Less than 60%
% reporting risks/safety concerns	None	See note 1	See note 1

The nature of reported risks and/or safety concerns could vary and include low, medium and high risks. On this basis, rather than specifying numbers for amber and red criteria, any reported risks/safety concerns will be discussed by the team and in conjunction with the Study Advisory Board to identify the extent to which they pose a concern in the context of decision making regarding a future definitive trial.

NRT, nicotine replacement therapy; SHS, secondhand smoke.

The decision on whether to progress to a definitive future trial will be guided by a combination of the progression criteria, important information learnt from the process evaluation questionnaire and the qualitative interviews and emerging evidence (eg, regarding the use of NRT products for temporary abstinence).

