**Methods and analysis:**

100 participants are being recruited through existing National Health Service (NHS) Lanarkshire initiatives and social media. Parents/carers who are at least 18 years old, smoke in the home and care for one or more children aged 0–16 years are eligible to take part. Participants are randomised to either the intervention (Group A) or control (Group B) arm. Group A receives NRT posted to their home for 12 weeks free of charge, alongside fortnightly telephone calls and materials to support them in reducing children’s exposure to SHS. Group B is signposted to the Scottish Government’s ‘Take it Right Outside’ website which provides interactive advice on creating a smoke-free home. To quantify the child’s exposure to SHS, participants instal an air quality monitor to measure fine particulate matter (PM_2.5_) concentrations in their living room for 7 days at baseline and 12-week follow-up and/or collect and post saliva samples from their youngest child (age 5 or over) for cotinine analysis. Qualitative interviews explore intervention experience, NRT use and adherence and changes to home-smoking behaviours/smoking-related expenditure. Descriptive data analyses will be performed to address the feasibility of recruitment, randomisation, retention and adherence, data collection and intervention delivery. Analysis will also include pre/post changes (paired t-test) in both child’s salivary cotinine and PM_2.5_ levels to provide preliminary data on intervention effectiveness and difference between the intervention and control arms of the study. Health economics and resource use data will be collected and assessed for completeness, to test the process of data collection and estimate mean cost of both study arms.

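### Table 1's recruitment criterion takes the number left after drop-out (35 per arm) as 100%, although the recruitment target is 100 participants, or 50 per arm

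*Protocol article*

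**What the plan says.** The Sample size section states the plan as follows: "we aim to recruit 100 participants, to have approximately 35 in each group (allowing for a 30% drop-out rate". The abstract repeats the target: "100 participants are being recruited". Allocation is equal. The end of the Eligibility criteria section says "Participants are randomised (1:1) to either the intervention (Group A) or control (Group B) arm".

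Table 1, in the section on pilot outcome measures and progression criteria, applies a traffic-light scheme. Its first row is expressed as the percentage of the sample size recruited. The highest level is "100% (35 in each arm", the middle level is "70% or more (25 in each arm", and the lowest is anything under 70%. A separate second row scores completed follow-ups for the secondhand smoke measures: 70%, 60–69%, and below 60%.

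The text after the table says that progression will be guided by these criteria combined with the process evaluation, the interviews and emerging evidence.

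**The concern.** The figure of 35 per arm has two roles. In the Sample size section it is what remains of 50 per arm after drop-out. In Table 1 it is full recruitment. These cannot both describe the same stage of the trial.

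Recruitment comes first in the primary objective, and Table 1 is the stated tool for judging it. If the row is applied as worded, a 30% shortfall against the target scores at the top level, and recruiting half the target scores at the middle level. Because the second row then takes its own percentage of whoever was recruited, both rows can be green while the number followed up falls well short of what the Sample size section set out to have.

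**Working it through.** **Inputs**
- Recruitment target 100, drop-out 30%, about 35 per group after drop-out (Sample size).
- 1:1 allocation (end of Eligibility criteria).
- Table 1, row 1: 100% is 35 per arm and 70% is 25 per arm.
- Table 1, row 2: 70% of follow-ups completed is the top level.
- Assumptions: the levels run green, amber, red in the order printed, and row 2's percentage is taken on those recruited.

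**Reproducing the plan's figure**
- Recruited per arm: 100 / 2 = 50. This figure is not printed; it follows from 100 and 1:1.
- Left after drop-out: 50 × (1 − 0.30) = 35 per arm. In reverse, 35 / 0.70 = 50 per arm, or 100 in total.

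The Sample size section is therefore consistent, and 35 is the post-drop-out number.

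**The base used in row 1**
- 0.70 × 35 = 24.5, shown as 25. Both counts in the row are built on 35, so this is a consistent choice of base and not an isolated slip.

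**The same counts against the recruitment target**
- Green: 35 / 50 = 70% of target (70 recruits).
- Amber: 25 / 50 = 50% of target (50 recruits).
- On a base of 50, 100% would be 50 per arm and 70% would be 0.70 × 50 = 35 per arm. The row's green count is thus the 70% level of the actual target.

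**What is left for analysis if the counts are recruits**

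| Recruited | Row 1 as worded | Followed up at 70% | Per arm |
|---|---|---|---|
| 100 | green | 100 × 0.70 = 70 | 35 |
| 70 | green | 70 × 0.70 = 49 | 24.5 |
| 50 | amber | 50 × 0.70 = 35 | 17.5 |

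In the second line rows 1 and 2 are both green, yet the number per arm is 30% below the planned 35 (24.5 / 35 = 0.70).

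**If the counts are retained participants**
- 35 retained per arm at 30% drop-out implies 50 recruited per arm. 25 retained implies 25 / 0.70 = 35.7, so 36 per arm. The figures of 24.5 and 17.5 then do not apply, because drop-out has already been taken off.

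**The case against.** The best defence is that the sample size is really 35 per group and 100 is only the intake needed to reach it. The Sample size section leans on "a median sample size per arm of 36 for pilot RCTs with similar primary outcome measures", which is close to 35, and row 1's arithmetic is sound on that base. On this view only the word for recruitment is loose, and the row means participants retained. Row 2 does not exclude this: it concerns secondhand smoke measures, and a participant can stay in the trial and answer the week-12 questions without completing one. A reader might infer that a retained meaning is impossible because drop-out would be scored twice. That goes too far; the rows would overlap but need not be identical.

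This part of the defence stands, but it does not rescue the text. The row is labelled as recruitment, the section lists enrolment and retention as separate quantities, and under the retained meaning no row would test recruitment against 100.

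Two other limits are fair. A reader might infer that the row by itself determines whether a definitive trial goes ahead, or that a shortfall would be hidden. The documents do not support either: the criteria are combined with other evidence, and the numbers screened, eligible, recruited and enrolled in the allocated time are all to be analysed. A pilot team may also deliberately set its green level below its intake aim. If so, the row should give that level as a percentage of the intake aim, not call it 100%.

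**Conclusion.** The inconsistency is real. A stated progression threshold labelled as recruitment uses the post-drop-out number as its base. Against the target of 100, the printed green count is 70% and the printed amber count is 50%. These percentages rest only on 100 participants and 1:1 allocation; keeping family members in the same arm may unbalance the groups slightly but does not change the base.

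The figures of about 24.5 and 17.5 per arm hold only if recruited is read literally and 70% are followed up. The retained meaning is less likely on the wording but remains possible, and it too requires a correction, to the label and by adding a recruitment row. The fault lies in the denominator or the label of one criterion. It does not show that the sample size is miscalculated or that the progression decision is fixed by this row.

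**What to change.** State which quantity row 1 measures, and correct it in one of two ways.

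1. If recruitment is meant, base the row on the target: 100% is 100 recruited (50 per arm), 70% is 70 recruited (35 per arm), and red is below 70. If the team wants green at fewer than 100 recruits, that is its choice, but the level should be printed as a percentage of 100.
2. If 35 and 25 per arm were meant as retained participants, relabel the row as retained, say at what time point, and add a recruitment row based on 100.

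The criteria were developed with the Study Advisory Group and recruitment began in January 2024, so the change should be agreed with that group, then dated and disclosed before progression is judged. The edit is one or two table rows. Its real cost is that green becomes harder to reach, and that a criterion is altered while the trial is under way, which is why the date and reason should be on record.
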